### Statistical analysis

Owing to the non-interventional study design, all ETNA-VTE-Europe data analysis will be explorative and descriptive only. In addition to the Europe-wide analysis, safety and effectiveness data will be presented for each individual country and region (Austria, Switzerland and Germany [DACH]; the United Kingdom and Ireland [UK/IE]; Belgium and the Netherlands [BE/NL]; and Italy). Comparisons between patients in particular edoxaban exposure categories (current use, recent use [within the last 3 days], and past use [> 3 days ago], as well as use within the last 30 days) will also be performed, with outcome data additionally presented for all patients permanently discontinuing edoxaban. Furthermore, subgroup analyses comparing patients with/without the following baseline characteristics are planned: renal impairment, hepatic impairment, DVT only (vs. PE with/without DVT), age ≥ 75 years, male gender, initial 30 mg edoxaban dose (vs. 60 mg), and active cancer.

To provide context to our results, the outcomes of ETNA-VTE patients will be appraised relative to those of PREFER in VTE patients treated with a DOAC, PREFER in VTE patients treated with a vitamin-K antagonist (VKA), Hokusai-VTE patients treated with edoxaban, and Hokusai-VTE patients treated with warfarin. These evaluations will be performed on an entirely visual basis, with no joint statistical models planned. Given the one-year follow up of the PREFER in VTE and Hokusai-VTE studies, only 12-month data from ETNA-VTE-Europe will be considered for these purposes [12, 13].

Data will be analysed and presented using descriptive statistics. Categorical variables will be reported as absolute numbers and percentages, and continuous variables will be presented as means with standard deviations or medians with interquartile ranges and minimum/maximum values, alongside the number of missing and non-missing observations. For select variables, 95% CIs will be provided. Where applicable, Kaplan-Meier analysis will be performed to illustrate risk over time. Time-to-event variables will be analysed using Cox proportional hazard regression and presented as hazard ratios with 95% CIs and *p*-values. The type of VTE (DVT only vs. PE ± DVT) will be included in all Cox models as an additional covariate. Based on the results of the Hokusai-VTE and the PREFER in VTE studies [6, 13], no further confounders will be considered at this stage, but any other relevant differences at baseline will be retrospectively added to the model.

A separate analysis combining 18-month safety data from ETNA-VTE-Europe and ETNA-AF-Europe will address the co-primary objective. Data will be presented as absolute and relative frequencies with 95% CIs, overall and for each aforementioned exposure category and subgroup. All statistical analyses will be performed using SAS® version 9.3 or higher (SAS Institute, Cary, NC, USA).

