## Background

Venous thromboembolism (VTE), which encompasses both deep-vein thrombosis (DVT) and pulmonary embolism (PE), has an annual incidence rate of approximately 104–183 per 100,000 person-years in individuals of European descent [1]. VTE is the third most common cardiovascular disease. The case-fatality rate is higher after PE than after DVT [2, 3]. Nevertheless, both events increase the probability of subsequent recurrent VTE, which affects approximately 17% of patients at 2 years, indicating that VTE is a chronic disease [4]. Consequently, effective anticoagulation to treat first-time VTE and prevent its recurrence is paramount.

Edoxaban is a direct oral anticoagulant (DOAC), which exerts its effects through inhibition of factor Xa. Based on results from the ENGAGE AF-TIMI 48 and Hokusai-VTE trials [5, 6], it was approved by the European Medicines Agency (EMA) regulatory for two main indications: the prevention of stroke/systemic embolism in patients with non-valvular atrial fibrillation (NVAF) with one or more risk factor, and the treatment/secondary prevention of acute VTE (DVT and/or PE) in adults [7]. However, current evidence for the safety and efficacy of edoxaban is derived from the patient populations enrolled in clinical trials. Furthermore, though current guidelines recommend that anticoagulation following VTE should be continued for at least 3 months and up to an indefinite duration, depending upon the risk of recurrence [8], no data currently exist for treatment with edoxaban beyond 12 months.

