### Objectives and outcome measures

The primary objective of ETNA-VTE-Europe is to quantify the long-term rate of VTE recurrence in a large, real-world population of acute symptomatic VTE patients prescribed edoxaban as part of their initial treatment regimen. Accordingly, the primary outcome measure will be the proportion of such patients who experience recurrent symptomatic VTE on one or more occasions within the 18 months following their index VTE, regardless of the length of edoxaban exposure.

The co-primary objective is to collect and evaluate real-world safety data regarding adverse drug reactions (ADRs) in patients treated with edoxaban across the currently approved indications. Therefore, ETNA-VTE-Europe data will be combined with 18-month safety data from the Edoxaban Treatment in routine cliNical PrActice for patients with non-valvular Atrial Fibrillation in Europe (ETNA-AF-Europe) study, a parallel European PASS evaluating the safety and effectiveness of edoxaban in real-world treatment of atrial fibrillation (AF) [10]. The outcome measure will be the proportion of patients who experience death (all-cause, cardiovascular, and VTE-related), bleeding events (major, clinically relevant non-major [CRNM], and minor bleeding; defined according to International Society on Thrombosis and Haemostasis [ISTH] criteria [11]), hepatic events, and/or other ADRs before the 18 month time-point in the two studies.

Secondary objectives are as follows: to evaluate the effects of persistent edoxaban use and permanent discontinuation on the rate of recurrent symptomatic VTE; to assess the rates of patient-relevant safety outcomes, including bleeding, ischaemic/haemorrhagic stroke, systemic embolic events (SEE), post-thrombotic syndrome (PTS), death, and hospitalisation due to cardiovascular causes; and to characterise the extent of adherence to edoxaban, reasons for and rate of discontinuation. To evaluate the effectiveness and safety of edoxaban relative to other anticoagulants, primary and secondary ETNA-VTE outcome data will be appraised in the context of those from the PREFER in VTE real-world registry and Hokusai-VTE clinical trial [12, 13]. The influence of study setting will also be explored by considering real-world ETNA-VTE data in the context of edoxaban data from the Hokusai-VTE clinical trial [12].

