### Potential limitations

As a prospective, non-interventional registry that aims to represent everyday occurrence and management of VTE, the stringent inclusion/exclusion criteria, physician/patient blinding, and site/protocol standardisation that typify RTCs do not apply. This introduces the possibility for biases that are difficult to avoid, measure or correct for. In particular, heterogeneous timing and length of edoxaban exposure may prove problematic for the interpretation of results, thought this will be taken into consideration at data analysis. Furthermore, in such a large-scale study, some incompleteness, insufficient detail, or inaccuracy of patient data is unavoidable; however, measures such as the careful design of case report forms and data monitoring/verification aim to minimise such occurrences. Despite the inherent limitations associated with observational registries, the all-inclusive nature of ETNA-VTE Europe may be seen as an advantage for obtaining a realistic snapshot of the clinical climate, with two-wave recruitment potentially allowing changes in treatment behaviour over time to be elucidated. Finally, while the single-arm nature of the study means that direct comparisons with other anticoagulants will not be possible, close accordance between the designs of PREFER in VTE and ETNA-VTE Europe should permit a reasonable appraisal of outcome differences.

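### The visual comparison with PREFER in VTE and Hokusai-VTE specifies no DVT/PE stratification or standardisation, so a different case mix could look like a drug difference

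*Protocol article*

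**What the plan says.** The Objectives section of the protocol article states the aim: "To evaluate the effectiveness and safety of edoxaban relative to other anticoagulants, primary and secondary ETNA-VTE outcome data will be appraised in the context" of the PREFER in VTE registry and the Hokusai-VTE trial. The Statistical analysis section names four reference groups (PREFER patients on a DOAC, PREFER patients on a VKA, Hokusai-VTE edoxaban, Hokusai-VTE warfarin), limits the comparison to 12 months, and fixes the method: "These evaluations will be performed on an entirely visual basis, with no joint statistical models planned".

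For regression within ETNA, the same section says: "The type of VTE (DVT only vs. PE ± DVT) will be included in all Cox models as an additional covariate". It then adds, citing the results of Hokusai-VTE and PREFER in VTE, that "no further confounders will be considered at this stage, but any other relevant differences at baseline will be retrospectively added to the model". DVT only versus PE with or without DVT is also one of the planned ETNA subgroups. The Background notes: "The case-fatality rate is higher after PE than after DVT".

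The Discussion says that the PREFER comparison will extend to particular patient subsets. It gives renal and hepatic impairment as examples and leaves the list open. Potential limitations concedes that a single-arm study cannot compare directly with other anticoagulants, but expects that the similarity of design to PREFER "should permit a reasonable appraisal of outcome differences".

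**The concern.** The plan treats VTE type as the factor to hold constant when patients are compared within ETNA. It says nothing about holding it constant when ETNA is set beside other studies, where the mix is under least control. Each cohort's PE share follows from its own eligibility rules and, in the registries, from prescribing choices. ETNA takes patients whose physician chose edoxaban, whereas PREFER recruited before edoxaban was in use.

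If the PE shares differ and the outcome depends on VTE type, overall rates will differ even when the drugs perform equally. Against PREFER or Hokusai-VTE warfarin, a reader would take this for a drug effect. Against Hokusai-VTE edoxaban, it would look like an effect of study setting, which the Objectives section also wants to explore. The figures at risk are those that readers will use to place edoxaban among the other anticoagulants.

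**Working it through.** **No figure of the plan to reproduce.** The article gives no number for the external comparison, no PE share for any cohort and no event rate by VTE type. Its sample size does reproduce: 1.96² × 0.08 × 0.92 / (0.15 × 0.08)² = 1963.4, so 1964. That concerns the primary rate, and only its 15% relative precision is used below, as a yardstick.

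**Crude ratio with no drug difference.** Let *a* and *b* be the PE shares of the two cohorts and *r* the event rate after PE divided by that after DVT, the same in both cohorts. The crude ratio of the second cohort to the first is

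(1 + b(r − 1)) / (1 + a(r − 1)).

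All values of *a*, *b* and *r* are assumptions.

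| PE shares | r = 1.5 | r = 2 | r = 3 |
|---|---|---|---|
| 40% vs 50% | 1.25/1.20 = 1.042 | 1.50/1.40 = 1.071 | 2.00/1.80 = 1.111 |
| 40% vs 60% | 1.30/1.20 = 1.083 | 1.60/1.40 = 1.143 | 2.20/1.80 = 1.222 |

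The spurious difference runs from about 4% to 22%. Which drug it favours depends on which cohort has more PE. Five of the six cases exceed 5%; one exceeds 15%.

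**Absolute scale, on assumed 12-month rates.**

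- 4% after DVT, 6% after PE, PE shares 40% vs 60%: 0.4 × 6 + 0.6 × 4 = 4.8% against 0.6 × 6 + 0.4 × 4 = 5.2%; ratio 0.92.
- 3% and 6%, PE shares 30% vs 60%: 3.9% against 4.8%; ratio 0.81.
- 6% after DVT, 4% after PE, PE shares 30% vs 60%: 5.4% against 4.8%; ratio 1.13. The direction reverses when DVT carries the higher rate.

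**Effect of standardising.** In the first case, weighting the ETNA stratum rates by the comparator's 60% PE share gives 0.6 × 6 + 0.4 × 4 = 5.2%, equal to the comparator, ratio 1.00. The other two cases also return to 1.00, because the stratum rates were set equal.

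**Against sampling error.** With 2700 × 0.75 = 2025 ETNA patients, all 3455 PREFER patients listed in Table 3 and an assumed 5% rate, the 95% half-width of the difference is 1.96 × √(0.05 × 0.95 × (1/2025 + 1/3455)) = 1.20 percentage points. It is wider for either PREFER treatment group alone. The spurious differences above (0.4 to 0.9 points) are smaller than this, but they do not shrink with more patients.

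**What the article says about direction.** The Background gives PE the higher case fatality. On recurrence it says only that both events raise the later risk. It does not say whether bleeding differs by VTE type.

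**The case against.** The strongest reply is that the article promises little here. All analysis is called explorative and descriptive, the outside data are there to give context, and direct comparison is said to be impossible. A DVT/PE subgroup is already planned in ETNA, and the Discussion's open list of PREFER subsets leaves room for a side-by-side DVT/PE display. Such tables are often detailed in a full protocol or SAP. PREFER's baseline VTE definition is the same as ETNA's in Table 2, and several regions overlap. The illustrated size rests wholly on assumptions.

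Much of this stands. A reader might infer that the comparison leaves out the DVT/PE split altogether. The article does not support that: the split is unspecified, not excluded. A reader might also infer that the plan breaks its own covariate rule. It does not, because that rule governs Cox models and none is planned for the outside comparison.

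The reply does not settle the matter. The method is stated, not left open, and stratified or standardised rates would be just as descriptive and need no joint model. The open list concerns PREFER only and does not name DVT/PE. A shared eligibility definition does not give equal PE shares. The sentence that concedes direct comparison is impossible goes on to expect a reasonable appraisal of differences.

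It is also true that splitting by VTE type repairs only part of the comparison. Hokusai-VTE's DVT stratum is proximal only, PREFER recurrences were not adjudicated, and bleeding definitions differ. A standardised rate shown without those caveats could look more adjusted than it is.

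**Conclusion.** The point holds as a worthwhile and inexpensive improvement; it does not show that the planned analysis is wrong. The objective is comparative, the stated method is visual, and the one confounder that the plan fixes in advance has no specified handling in the outside comparison.

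The size cannot be computed from the article. The range of about 4-22% holds only for assumed PE shares of 40% against 50-60% and PE/DVT event ratios of 1.5 to 3. It would be tempting to conclude that recurrence or bleeding will be biased in a known direction, but the article supports a direction for mortality alone.

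**What to change.** In the Statistical analysis section, specify the 12-month comparison as follows.

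- For each of the four reference groups, show results separately for DVT only and for PE with or without DVT.
- Beside the crude overall rate, show the ETNA rate directly standardised to that comparator's DVT/PE mix, with its 95% CI.
- For both Hokusai-VTE groups, first leave out ETNA patients with isolated distal DVT, since Hokusai-VTE excluded them (Table 2 and Discussion).
- Where a comparator has no results by VTE type, report the crude figure as context only and do not interpret it as an outcome difference.
- State that differences in adjudication, bleeding definitions and eligibility remain after standardisation.

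The cost is a few table columns and a weighted average, with no joint model and no new data collection. Intervals within strata will be wider, and the fix depends on comparator results by VTE type, whose availability the article does not show.

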### Sample size calculations

Assuming an overall 18-month symptomatic VTE recurrence rate [12, 13] of 8.0% in patients who receive edoxaban (regardless of treatment discontinuation) and a relative precision of 15% for a two-sided 95% confidence interval (95% CI), data for 1964 patients will be required to assess with sufficient accuracy the primary outcome. Given an expected dropout rate of 25%, enrolment of 2700 patients should result in an adequate sample size for evaluation at 18 months.

In order to obtain a dataset as large as possible for co-primary outcome assessment, safety data from ETNA-VTE-Europe will be combined with 18-month safety data from ETNA-AF-Europe, a sister European PASS study of edoxaban in approximately 13,100 patients with NVAF [10]. Together, these studies will enrol approximately 15,800 patients, with an overall expected 18-month dropout rate of 20%. Consequently, data for approximately 12,640 patients should be available at 18 months to assess the incidence rates of interest and their 95% CIs. A key aim of this combined analysis is to provide sufficient statistical power to capture uncommon ADRs with low incidence rates; for those that occur at rates of 0.1–1.0%, the corresponding precision of 95% CIs will range from ±0.06% to 0.17%.

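### If the Kaplan-Meier curves cover recurrence or bleeding with deaths censored, they overstate risk: slightly overall, materially only where mortality is high

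*Protocol article*

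**What the plan says.** The Statistical analysis section makes two statements about time-to-event data. On curves: "Where applicable, Kaplan-Meier analysis will be performed to illustrate risk over time". On models: "Time-to-event variables will be analysed using Cox proportional hazard regression and presented as hazard ratios with 95% CIs". No other method for displaying risk over time is named. The text does not list the endpoints that get a curve or say what happens to a patient who dies.

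The headline results are defined differently. Under Objectives and outcome measures, the primary outcome is "the proportion of such patients who experience recurrent symptomatic VTE on one or more occasions within the 18 months following their index VTE", whatever the length of edoxaban exposure. For the co-primary safety analysis, the Statistical analysis section says: "Data will be presented as absolute and relative frequencies with 95% CIs, overall and for each aforementioned exposure category and subgroup".

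Death is a reported outcome in its own right (all-cause, cardiovascular and VTE-related), and Table 1 has it recorded throughout follow-up. Entry criteria are minimal. The planned subgroups include age 75 years or over and end with "initial 30 mg edoxaban dose (vs. 60 mg), and active cancer". The article gives no expected mortality, overall or by subgroup.

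**The concern.** A patient who dies can no longer have a recurrence or a bleed. Kaplan-Meier with deaths censored treats that patient as if still at risk beyond the date of death. One minus the curve then estimates a hypothetical risk with death removed, and it is never below the proportion of patients who actually have the event. The primary outcome is that actual proportion, so a recurrence curve built this way would have a different estimand from the result it is meant to illustrate.

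The gap grows with mortality. The cohort is largely unselected and one planned subgroup is active cancer, so the curves could overstate absolute risk most where readers look closely. The Sample size calculations section expects 25% dropout. A curve uses partial follow-up, so some readers may take their 18-month risk from it rather than from the proportion. The comparisons with the earlier registry and trial are to be made by eye. If curves are used there, differences in mortality between the populations would enter the comparison.

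**Working it through.** **1. The plan's own figure.** The Sample size calculations section starts from "Assuming an overall 18-month symptomatic VTE recurrence rate [12, 13] of 8.0% in patients who receive edoxaban" and "a relative precision of 15% for a two-sided 95% confidence interval (95% CI), data for 1964 patients will be required". The half-width is 0.15 × 8.0% = 1.2 percentage points. Then n = 1.96² × 0.08 × 0.92 / 0.012² = 1963.4, rounded up to 1964, so the stated figure reproduces. Enrolling 2700 with 25% dropout leaves 2025 patients. The ±1.2 points serve below as a yardstick.

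**2. Formula, constant hazards.** Let c be the true proportion with the event by 18 months, and m the proportion dying first. Let L and D be the cumulative hazards of event and death to 18 months. Then c + m = 1 − exp(−(L + D)) and c/(c + m) = L/(L + D). So L = −ln(1 − c − m) × c/(c + m), and one minus Kaplan-Meier with deaths censored is 1 − exp(−L).

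- c = 8%, m = 10%: L = 0.1985 × 0.08/0.18 = 0.0882, and the curve reads 8.4%.
- c = 12%, m = 40%: L = 0.7340 × 0.12/0.52 = 0.1694, and the curve reads 15.6%.

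Only the 8% comes from the article. The 12% and every value of m are assumptions.

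| True proportion c | Dying first m | Curve reads | Excess (points) | Relative excess |
|---|---|---|---|---|
| 8% | 2% | 8.1% | 0.08 | 1% |
| 8% | 5% | 8.2% | 0.21 | 3% |
| 8% | 10% | 8.4% | 0.44 | 6% |
| 8% | 15% | 8.7% | 0.69 | 9% |
| 12% | 40% | 15.6% | 3.6 | 30% |
| 12% | 50% | 17.1% | 5.1 | 42% |

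**3. Sensitivity to timing.** Early recurrences leave less time for death to intervene. Put half of L in the first 3 months, so that the monthly event hazard is h1 = L/6 and then h2 = L/30, with a constant death hazard d = D/18. With A = (1 − exp(−3(h1 + d)))/(h1 + d) and B = exp(−3(h1 + d)) × (1 − exp(−15(h2 + d)))/(h2 + d), solve h1·A + h2·B = c and d(A + B) = m numerically.

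- c = 8%, m = 10%: the curve reads 8.3% (4% relative).
- c = 12%, m = 40%: L = 0.1537, and the curve reads 14.2% (19% relative).
- c = 12%, m = 50%: L = 0.1637, and the curve reads 15.1% (26% relative).

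**4. Subgroup contrasts.** The direction depends on which group has the higher event rate. The first formula, with all inputs assumed, gives:

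- High-mortality group has more events: 12% (40% dying first) against 7% (4% dying first). The true ratio is 12/7 = 1.71. The curves read 15.6% and 7.15%, a ratio of 2.18, so the contrast is widened.
- High-mortality group has fewer events: 7% (40% dying first) against 12% (4% dying first). The true ratio is 7/12 = 0.58. The curves read 9.0% and 12.3%, a ratio of 0.74, so the contrast is narrowed.

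**The case against.** The strongest reply is that the article does not say what the concern needs it to say. It names no endpoint for the curves, states no censoring rule and promises no curves by subgroup. All-cause death, for which Kaplan-Meier is appropriate, is among the outcomes, so the clause could be read as covering that alone. The article condenses a fuller protocol, and the statistical analysis plan is not shown. Either may already deal with death, and silence here is not an error. This stands, and it makes the point conditional. It does not remove the point, because the text does choose a method, and by default that method censors deaths.

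Second, the absolute risks that the study reports as its main results are proportions and frequencies, and the section describes all analyses as exploratory and descriptive. This also stands: the curves are illustrative. Nor would a gap between a curve and the crude proportion be evidence of this bias alone, since 25% dropout can produce one too.

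Third, some deaths are events and not censoring. The major-bleeding definition in Table 2 includes fatal bleeding. That is correct, and the fix has to respect it.

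Fourth, at cohort level the effect is small. At 10% dying first it is about 0.4 points, well inside the ±1.2 points on which the study was sized. That is also correct.

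**Conclusion.** The point holds in conditional form. If Kaplan-Meier with deaths censored is used for recurrence, bleeding or similar events, the curves lie at or above the actual risk. For up to 10% dying first the overstatement is about 1 to 6% relative and would not change any reading of the cohort. At 40% dying first it is about 20 to 30% relative, the lower end applying if recurrences come early. The mortality figures and the 12% recurrence are assumptions, because the article gives only the 8.0%.

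A reader might infer more, and the document does not support it:

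- That the plan states deaths will be censored. It does not; this is the standard behaviour of the method named.
- That the curves would be badly wrong in patients with active cancer and in those aged 75 or over. For active cancer this requires high mortality, which is plausible but not documented. For the older group there is no basis for a size.
- That subgroup differences would be exaggerated. The second contrast in step 4 shows that they can equally be narrowed.
- That the primary or co-primary results or the sample size are affected. They are not.

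**What to change.** Replace the Kaplan-Meier sentence for events that death can preclude. For recurrent VTE, bleeding, stroke or systemic embolism, and post-thrombotic syndrome, show the Aalen-Johansen cumulative incidence with death as a competing event. Deaths that belong to the endpoint count as events: fatal bleeding does, and so does fatal PE if it is counted as a recurrence. Keep Kaplan-Meier for all-cause death. State that the Cox hazard ratios for these endpoints are cause-specific. If the full protocol or the statistical analysis plan already does this, confirming it is enough.

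The cost is minor extra programming with a standard procedure, and curves that read slightly lower. Deaths are already collected, so no new data are needed, and the sample size stays as it is.

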PTS^(9)^	X		X		X	X	
Vital signs^(10)^	X	X	X	X	X	X	
Laboratory parameters^(9)^	X	X	X	X	X	X	
ADRs^(11)^	X	X	X	X	X	X	

*Legend:* VTE, venous thromboembolism; PTS, post-thrombotic syndrome; ADR, adverse drug reaction; LPO, last patient out. ^(1)^ Confirmed first or recurrent VTE within the 2 weeks preceding enrolment; treated with edoxaban according to Summary of Product Characteristics; written informed consent; no simultaneous interventional study participation. ^(2)^ Age and gender, alcohol consumption, smoking status, frailty, comorbidities, and medical history. ^(3)^ Details of past and current VTE risk factors, symptoms, diagnosis, interventions, treatment, and related clinical events (stroke, bleeding events, systemic embolism, non-valvular atrial fibrillation, and malignancies). ^(4)^ History and current status, including dose, prescription intervals, and any changes to edoxaban treatment since last data point (including permanent discontinuation, in which case date, reason and subsequent therapy must be provided). ^(5)^ Physician judgment only. ^(6)^ Timing, diagnosis and interventions. ^(7)^I.e. death, stroke, bleeding events, systemic embolism, non-valvular atrial fibrillation, and malignancies. ^(8)^ Admittance and discharge dates, clinical event, and use of the emergency room and/or intensive care unit. ^(9)^ If assessed. ^(10)^ Including blood pressure, heart rate, height and weight. ^(11)^ As per the Guideline on Good Pharmacovigilance Practices (GVP) Module VI (Management and reporting of adverse reactions to medicinal products; EMA/873138/2011 Rev. 1) [16]; coding according to the standardised Medical Dictionary for Regulatory Activities (MedDRA).*Defined as the first day of heparin administration after the index acute VTE event. ^†^Since 18-month time point. ^§^Changes in symptoms/diagnosis and any other VTE-relevant information

Upon completion of the ETNA-VTE-Europe registry, data will be extracted for the following time points: baseline, 1, 3, 6, 12 and 18 months. Details of the parameters to be evaluated at each time point are outlined in Table 1. The current status, change/events since baseline and change/events since the previous time point will be assessed for each parameter, as appropriate. In addition, recurrence of symptomatic VTE and death since the 18-month time point will be retrospectively documented at the time of LPO per country.

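### Cox models fix VTE type as the only covariate and add others retrospectively under no stated rule, leaving secondary hazard ratios liable to confounding and to data-driven adjustment

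*Protocol article*

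**What the plan says.** All references are to the protocol article.

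- **Model (Statistical analysis).** "Time-to-event variables will be analysed using Cox proportional hazard regression and presented as hazard ratios with 95% CIs", together with p-values.
- **Fixed covariate (same section).** "The type of VTE (DVT only vs. PE ± DVT) will be included in all Cox models as an additional covariate".
- **Other covariates (same section).** Citing the results of Hokusai-VTE and PREFER in VTE, the article states that "no further confounders will be considered at this stage, but any other relevant differences at baseline will be retrospectively added to the model".
- **Contrasts (same section).** "Comparisons between patients in particular edoxaban exposure categories (current use, recent use [within the last 3 days], and past use", plus use within the last 30 days. In addition, "subgroup analyses comparing patients with/without the following baseline characteristics are planned"; that list includes renal impairment, age 75 or over, and "initial 30 mg edoxaban dose (vs. 60 mg), and active cancer".
- **Objective served (Objectives and outcome measures).** A secondary objective is "to evaluate the effects of persistent edoxaban use and permanent discontinuation on the rate of recurrent symptomatic VTE".
- **Data available (Table 1 legend).** Baseline characteristics are "Age and gender, alcohol consumption, smoking status, frailty, comorbidities, and medical history". VTE risk factors and malignancies are recorded as well. Laboratory parameters are recorded only where they were assessed.
- **Status (Statistical analysis).** All analysis is described as exploratory and descriptive.

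**The concern.** Treatment is left wholly to the physician and patient (Patient recruitment), so who stops edoxaban, and who starts on which dose, will depend partly on prognosis. The article treats age, renal impairment and active cancer as important enough for subgroup analyses but fixes none of them for adjustment.

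Selecting confounders by the baseline differences that turn up has two weaknesses. A strong prognostic factor with a modest imbalance may not look relevant and be left out. And if the selection is made with outcomes in view, it can follow the result, while the reported intervals and p-values behave as if the model had been fixed in advance.

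At stake is the reading of the hazard ratios that would answer the persistence and discontinuation objective. The Conclusions promise essential information on how treatment duration and discontinuation affect outcomes, so readers will look to them.

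**Working it through.** **1. Does the cited justification support the rule?** By the article's own account, only weakly. The Discussion says Hokusai-VTE excluded isolated distal DVT, creatinine clearance below 30 mL/min and significant liver disease, so it cannot show that these do not confound here. Table 3 places PREFER in VTE before edoxaban, so it cannot show what drives edoxaban dosing or stopping.

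**2. Can the rule be carried out?** In a single-arm study a baseline difference needs two named groups, and the rule names none. Current, recent and past use are states entered after baseline, and one patient can pass through all of them. No baseline groups exist for that contrast.

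**3. Planning figures, reproduced first.** Inputs from Sample size calculations: p = 0.08, relative precision r = 0.15, two-sided 95% CI, dropout 25%, enrolment 2700.

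- n = z²(1−p)/(p·r²) = 3.8415 × 0.92/(0.08 × 0.0225) = 1963.4, rounded up to 1964, as stated.
- 1964/0.75 = 2619, and 2700 × 0.75 = 2025. The sample size is sound.

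**4. Expected recurrences.**

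- Among completers: 0.08 × 1964 = 157, or 0.08 × 2025 = 162.
- Counting events before dropout, assuming constant hazards for both: cumulative hazards over 18 months are −ln 0.92 = 0.0834 and −ln 0.75 = 0.2877. The observed-event probability is 0.0834/(0.0834 + 0.2877) × (1 − 0.92 × 0.75) = 0.0697, giving 0.0697 × 2700 = 188.
- Seven covariates at one degree of freedom each leave 157/7 ≈ 22 to 188/7 ≈ 27 recurrences per covariate. The article gives no expected counts for bleeding or death.

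**5. Illustration of size (all inputs assumed).** For one omitted binary confounder with hazard ratio HR and prevalences p1 and p0 in the two groups, a true hazard ratio of 1.0 is multiplied by [1 + p1(HR−1)]/[1 + p0(HR−1)]:

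| Confounder HR | 20% vs 10% | 40% vs 10% | 60% vs 20% |
|---|---|---|---|
| 1.5 | 1.05 | 1.14 | 1.18 |
| 2 | 1.09 | 1.27 | 1.33 |
| 3 | 1.17 | 1.50 | 1.57 |

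The chance of p < 0.05 with no true effect follows from SE(log HR) = 1/√(events × a(1−a)). With 162 events and a smaller-group share a of 10% or 20%, the SE is 0.262 or 0.196. For a factor of 1.27 and a = 10%: ln 1.27/0.262 = 0.91, and 1 − Φ(1.96 − 0.91) + Φ(−1.96 − 0.91) ≈ 0.15.

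| Bias factor | a = 10% | a = 20% |
|---|---|---|
| 1.09 | 6.2% | 7.2% |
| 1.18 | 9.7% | 13.4% |
| 1.27 | 15.0% | 22.9% |
| 1.57 | 40.6% | 63.2% |

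The SE formula treats exposure as a fixed binary factor, which is a simplification for changing use. The left-hand column of the first table bears most closely on the stated rule, because large imbalances would probably be noticed and added.

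**The case against.** **The analyses are labelled exploratory, the limitations are admitted, and a covariate list normally belongs in the analysis plan.** This stands in part. Potential limitations does acknowledge biases that are hard to correct and names heterogeneous exposure, and the reference to the present stage leaves room for later specification. But the article does more than stay silent: it states a rule, and the rule is retrospective selection. The exploratory label softens the error-rate concern. It does not remove confounding, and p-values are still to be reported.

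**The article never ties a Cox model to a particular contrast.** Correct. The link is an inference: a hazard ratio in a single-arm cohort needs a within-cohort comparison, and the article lists these ones. It is plausible for persistence and exposure category. It is weaker for initial dose, which appears only among baseline characteristics for subgroups. A reader might infer that a dose-effect hazard ratio is planned; the text does not say so.

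**The plan does not stop at VTE type.** Also correct. It commits to further adjustment. What it lacks is the content and timing of that adjustment.

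**A large bias cannot be claimed.** This stands. A reader might combine two strong confounders, say active cancer at 15% against 5% with HR 3 (1.30/1.10 = 1.18) and provoked VTE at 20% against 50% with HR 0.5 (0.90/0.75 = 1.20), to reach 1.42. Every input is assumed, both biases are made to point the same way, independence is required, and imbalances that large are ones the retrospective rule would probably catch.

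**Conclusion.** The point holds as a weakness of the secondary, exploratory Cox analyses. The article commits itself to one fixed covariate and an undefined retrospective addition for contrasts formed by choice. The resulting hazard ratios are liable to confounding by indication, and their p-values and intervals do not account for the selection of covariates. For initial dose this rests on inference.

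A reader might go further and conclude that the hazard ratios are confounded by a known amount, or that the main results are compromised. The documents support neither. Size and direction are unknown; the factors of 1.05 to 1.57 depend on assumed prevalences and effects. The primary outcome is a single-arm proportion and the co-primary analysis reports frequencies with confidence intervals, so neither needs a Cox model. The sample size reproduces exactly.

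**What to change.** Replace the sentence on further confounders with a set chosen on subject-matter grounds and fixed before outcomes are examined: age, sex, active cancer, renal function, previous VTE, provoked or unprovoked index event, and VTE type. State which contrasts are to be modelled. State a reduced set for bleeding and death models where events are few.

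Model current, recent and past use as time-dependent exposure. Baseline covariates alone will not deal with reasons for stopping that arise during follow-up, and the report should say so. Give unadjusted and adjusted results together, and label any covariate added later as a sensitivity analysis.

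The cost is modest but more than a wording change. Most of these variables can be drawn from the baseline items in Table 1. Renal function presumably comes from laboratory parameters, which are recorded only if assessed. The rule under Quality control that omits patients with missing observations would then let each covariate change who is analysed, so these models need imputation in its place. Time-dependent exposure also needs dated changes in edoxaban use; Table 1 already requires a date for permanent discontinuation. Enrolment does not change.
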